#### Secondary outcomes

Table 2 shows all patient/oncologist-reported outcomes, including the instruments used and the timing of assessments.

**Table 2 Tab2:** Secondary outcomes self-reported by patient or oncologist

Concept	Instrument	Patient					Oncologist		
		T0	T1	T2	T3	T4	T0	T1	T2
Perceived communication efficacy	Purpose designed		x						
Evaluation of communication and decision making in consultation									
Satisfaction with communication	PSQ with one extra item on SDM			x			x^a^	x^a^	x
Perceived oncologist empathy	Purpose designed items			x					
	Purpose designed VAS			x					x
Preferred/perceived decisional role	CPS		x	x					
Patient-reported SDM	SDMQ-9			x					
Decision evaluation	DCS			x					
Trust in the oncologist	Two items from TiOS			x					
Distal outcomes									
Attitudes towards striving for quantity (length) or quality of life	QQQ			x	x	x			
Quality of life	EORTC-QLQ C30	x			x	x			
Potentially adverse outcomes									
Anxiety	STAI	x		x	x	x			
	+ 1-item VAS scale	x	x	x	x	x			
Fighting spirit	Mini-MAC subscale	x		x	x	x			
Helplessness/Hopelessness	MAC subscale	x		x	x	x			
Use and evaluation of communication aid									
Use of the communication aid	Purpose designed				x^b^	x^b^			
Evaluation of the communication aid	Purpose designed			x^b^	x^b^	x^b^			

PSQ Patient Satisfaction Questionnaire, CPS Control Preferences Scale, SDMQ-9 Shared Decision Making Queationnaire −9 items, DCS Decisional Confict Scale, TiOS Trust in Oncologist Scale, QQQ Quantity Quality Questionnaire, EORTC-QoL-C30 European Organization of Research and Treatment of Cancer Quality of Life Questionnaire, STAI Spielberger State and Trait Anxiety Inventory, MINI-MAC Mini Mental Adjustment to Cancer scale, MAC Mental Adjustment to Cancer scale. ^a^ Satisfaction with communication in simulated encounter. ^b^ For patients randomized to receive the communication aid only

A. Immediate outcomes related to communication and decision makingTo assess observed SDM in a simulated setting (before and after training), oncologists will engage in standardized patient assessments both before and after training in the intervention group and on two occasions over a period of 12–16 weeks in the control group. Two standardized patients will be trained with the use of script. These scripts reflect a patient with metastatic gastric cancer (T0) and a patient with metastatic esophageal cancer (T1) who meet with the oncologist to discuss the start of first-line palliative chemotherapy. Two experienced standardized male patients will be educated about SDM, and instructed to act in a standard way and to be rather passive and not overly emotional during the encounter. They will be taught to ask a set of standard questions in all consultations, and to apply a limited set of ‘if ….then’ rules, e.g., certain questions to ask only in case the oncologists present a choice between chemotherapy and best supportive care. They will be instructed about their preference (and the underlying values and reasoning) in case a choice was presented to them, which in both cases was to prefer chemotherapy. Oncologists will receive a simulated medical file prior to the consultation, containing the standard medical information available to them prior to first patient contact. Both the script and the medical file were developed in a multidisciplinary team including psychologists and a medical oncologist, and were adjusted on the basis of experience in the pilot study (see Interventions, Oncologist training). Oncologists will be asked about their opinion on how realistic the simulated consultation was with 2 items with Likert scale responses (1–10) specifically designed for this study. The level of SDM in the simulated consultations will be assessed with the same instruments as described above.Observed general communication skills will be assessed in both simulated encounters and in actual encounters in clinical practice. Two items are to be rated by the two coders (double coding for all consultations): one assessing the quality of information giving (using skills like inviting questions, structuring information, summarizing) and one assessing the quality of responding to or anticipating patient’s emotional responses (using skills like showing empathy, silences, reflecting on emotions). Both items are rated on a 5-point scale ranging from 0 ‘not or hardly visible’ to 4 ‘very frequently’, and a score of 2 representing ‘sufficient’.Patients’ perceived efficacy in communication will be assessed with four items measuring perceived efficacy in questions asking and communicating values and preferences prior to the consultation. The items were purposefully designed for this study. Patients provide answers on VAS scale.To assess patient and oncologist satisfaction with communication in the consultation we will use the 5-item Patient Satisfaction Questionnaire (PSQ) [74], with a modified version for oncologists [75]. In both versions, an item about satisfaction with patient involvement in decision making was added.Patient-reported empathy in the consultation (post-consultation) will be assessed with one item asking about overall perceived empathy on a VAS scale as well as an adapted 5-item version of the empathy scale used in earlier research [76] with 5 response categories. Oncologist perceived empathy will be assessed with the same 1-item VAS scale as used for patients.To assess congruence between preferred and perceived role in decision making, patients’ preferred (before consultation) and perceived role (after consultation) will be assessed with the widely used one-item Control Preferences Scale (CPS) [77]Patient-reported shared decision making will be assessed with the validated 9-item Shared Decision Making Questionnaire (SDMQ-9) [78, 79].Patients’ decision evaluation will be assessed with the 16-item Decisional Conflict Scale [80, 81], a widely used scale to assess patient’s uncertainty about medical decisions. The formulation of the last three items is slightly adapted (‘my’ decision into ‘this’ decision).Patients’ trust in the oncologist (after consultation) will be assessed with the two overall items of the Trust In the Oncologist Scale [82, 83].

B. Distal outcomes:The treatment decision made will be registered from the medical record and categorized (starting, foregoing, (dis)continuing, adjusting palliative systemic treatment).Patients’ attitudes towards striving for quantity (length) or quality of life will be assessed with the 8-item Quality Quantity Questionnaire (QQQ) [84]Patients’ quality of life will be assessed with the 30-item EORTC Quality of Life Questionnaire (EORTC-QLQ C30) [85], a health-related quality of life questionnaire which is specifically designed and validated for cancer patients.

C. Potentially adverse outcomes:Anxiety will be assessed with the validated 6-item short version of the state scale of the Spielberger State and Trait Anxiety Inventory [86], as well as a 1 item VAS scale [87]. The pre-consultation (waiting room) questionnaire (T1) will only contain the 1-item VAS scale.Fighting spirit will be assessed with the 4-item subscale of the Mini Mental Adjustment to Cancer (MAC) scale [88]. Of note, a loss of fighting spirit is labelled as an adverse outcome, yet it could similarly be argued that accepting instead of fighting the disease is a more adaptive coping response on the long term, particularly in case of advanced cancer.Helplessness/hopelessness, will be assessed with the 6-item subscale of the original Mental Adjustment to Cancer (MAC) scale [89, 90].

D. Consultation duration and patients’ use and evaluation of the communication aid

Consultation time will be registered on the basis of the audiotape. Patients’ use of the communication aid will be monitored by asking if and how patients have used the tool since the recorded consultation (T3) or in the past three months (T4). Furthermore, patients’ evaluation of the aid will be assessed with 8 items developed for the current study about the perceived usefulness of the tool in e.g., asking questions and making decisions.

#### Background characteristics

Patients will be asked for their date of birth (age) by telephone. In the patient baseline survey (T0), their personal living situation, number of children (less than 18 years old), religion, nationality, educational level and preference for information with 1 item [91] will be assessed. In the oncologist baseline survey (T0; after the first standardized patient assessment), oncologists will be asked for their date of birth, years of experience, number of palliative cancer patients they see per month, communication training experience, their role preference in decision making (their patients’ preference and their own preference with the CPS [92]) and personal death attitude (3 selected items from the Death Attitude Profile-Revised [93]).

### Statistical methods

#### Primary outcome

To account for the hierarchical nature of the data, i.e. patients nested within oncologists, multilevel regression analysis will be used to test the effect of the single interventions on the observed level of SDM in the audio-recorded consultation. Analysis will be conducted separately for the OPTION12 and the 4SDM. Random intercept and slope models will be examined. The effect of the oncologist training (level of oncologists) will be established among patients who did not receive a communication aid. The effect of the communication aid (level of patients) will be established among patients of untrained oncologists. Effects with two-sided *p*-values < .05 will be considered significant; 95CI’s as well as effect sizes will be provided. As the OPTION12 is currently the most widely used instrument to assess SDM, an intervention will be considered effective if it had a significant effect on OPTION12 scores. Baseline differences across arms on background characteristics (patient age, gender, educational level) as well as patients’ baseline measures will be examined with the appropriate statistical tests (ANOVA, Chi-squared tests). All analyses of effectiveness will be controlled for differences between arms at baseline as well as the two stratification variables (working status oncologist, type of consultation). All analyses will be intention-to-treat, i.e., all eligible consultations will be included in the analysis (irrespective of whether the communication aid was actually received or read; or whether the oncologist received the full training package).

The hypothesized additional effect of the combined intervention will most likely be smaller than the effects of the single interventions (RQ1). That is, combining the two is hypothesized to increase but not to double the effect of the single interventions. The combination of the training and the aid will be considered more effective than either or both single interventions if (1) the effect size of the combination compared to care as usual is statistically significant and (2) is at least 150% of the effect size of either or both single interventions. The study is not powered to statistically test the difference between the combination and the single interventions.

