### Sample size

The trial is powered to detect an independent effect of the two interventions on observed SDM, as assessed with the OPTION12 [62, 63], a widely used instrument to assess SDM in consultations. There is no agreement on what constitutes a clinically meaningful difference on the OPTION12. The sizes of the effects of SDM interventions on OPTION12, including decision aids and physician training across different specialties and in both simulated and clinical settings, range from 0.5 to 1.5 [41, 64, 65]. As most reported large effect sizes, we adopted an effect size of d = 0.8 in the sample size calculation. We expected that the effect of the combination of the oncologist training and the patient communication aid will be larger, but not twice as large (estimated effect size = 1.2). To account for this hypothesized antagonistic interaction [66], we decided to adopt a parallel group design instead of a factorial design. Hence, we will examine the effect of the oncologist training among patients allocated to the control condition (between-oncologist comparison) and the effect of the patient communication aid among untrained oncologists (within-oncologist comparison).

SDM will vary by oncologist. ICC’s for the OPTION12 reported in literature [67, 68] and personal communication ([name], Leiden University, the Netherland, May 2014; [name], University Medical Center Hamburg, Germany, July 2014) range from 0.11 to 0.60. In a sample of 47 audio-recorded consultations meeting the same eligibility criteria as the current trial [20], an ICC of 0.19 for OPTION12 scores was demonstrated (unpublished). Since the ICC was 0.20 or lower in the majority of these data sets, a value of 0.20 was adopted in the sample size calculation.

Sample size calculation was based on the effect of the oncologist training (between-oncologist comparison; two-sided t-test taking into account clustered data). The above mentioned criteria, along with a power of >80% and α of 0.05, resulted in a required sample size of 24 oncologists and 192 patients (12 oncologists per arm and 8 patients per oncologist; power = 0.84).

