### Procedure and time line

Figure 1 shows the time line for oncologists and patients. *Oncologists* will participate in a simulated encounter with an actor patient (standardized patient assessment) at two points in time, with 2–3 months in between. After each assessment they will complete a questionnaire (T0 and T1). Oncologists randomized to the training condition will receive the skills training between the first and second standardized patient assessment. Subsequently, for each oncologist, we aim to audio-record consultations with 8 patients in daily clinical practice with a small audio-recording device. Either a research associate or the oncologist will operate the recorder. The research associate will not attend the consultation. After each consultation, oncologists complete a short questionnaire (T2).

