#### Secondary outcomes

The effect of the interventions on the secondary outcomes will be analyzed in multi-level regression analysis with either 2 or 3 levels, i.e., outcome assessment at different time points (level 1; if applicable), nested within patients (level 2) nested within oncologists (level 3). The effect of the training on the observed level of SDM and general communication skills in simulated patient encounters will be assessed by using a repeated measure ANOVA with time (within subjects, effect of time), condition (between subjects, effect of condition) and time x condition (effect of the training) as independent variables. To present patients’ use and evaluation of the communication aid, the appropriate descriptive statistics will be used (medians, percentages).

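### Each oncologist's pre-training SDM score is collected but is not a named covariate in the training comparison, and the simulated-encounter analysis uses it only as a change score: valid, but less efficient than it could be

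*Protocol article*

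**What the plan says.** Under Procedure and time line, all oncologists have two standardized patient assessments before their clinic consultations are recorded. Those in the training arm "will receive the skills training between the first and second standardized patient assessment". Under Secondary outcomes, part A: "The level of SDM in the simulated consultations will be assessed with the same instruments as described above". Each oncologist therefore has a pre-training OPTION12 and 4SDM score.

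Under Statistical methods, Primary outcome, "The effect of the oncologist training (level of oncologists) will be established among patients who did not receive a communication aid". The model adjusts for two stratification variables (the oncologist's working status and the type of consultation) and for whatever differs between arms at baseline. The baseline variables named there belong to patients: age, gender, education and patients' own baseline measures. The oncologist's first simulated score is not named.

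Under Statistical methods, Secondary outcomes, the effect of training in the simulated encounters "will be assessed by using a repeated measure ANOVA with time", condition and their interaction, and the interaction is taken as the training effect.

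Under Sample size: "Sample size calculation was based on the effect of the oncologist training (between-oncologist comparison; two-sided t-test taking into account clustered data"). The inputs are "we adopted an effect size of d = 0.8 in the sample size calculation" and, for the ICC, "a value of 0.20 was adopted in the sample size calculation". The reported ICCs "range from 0.11 to 0.60".

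**The concern.** The comparison that sizes the trial sets 12 oncologists against 12. With about four no-aid patients per oncologist, half of the variance of an oncologist's mean lies between oncologists. Patient covariates are not aimed at that half. A pre-training score on the primary instrument is, and the trial already collects it. Naming it in advance could sharpen the training estimate, and likewise the estimate for the combination against usual care. The communication-aid comparison is within oncologists and gains little.

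In the simulated encounters, a change score fixes the coefficient of the first score at 1, whereas ANCOVA estimates it. With 24 oncologists and one encounter each per time point, the difference in precision is not trivial.

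**Working it through.** **Reproducing 0.84.** Inputs from Sample size: d = 0.8, ICC = 0.20, 12 oncologists per arm, 8 patients each, two-sided alpha 0.05. Only no-aid patients enter, so about m = 4 per oncologist.
- Variance of an oncologist mean: 0.20 + 0.80/4 = 0.40.
- Standard error of the difference: sqrt(2 × 0.40/12) = 0.258.
- Noncentrality: 0.8/0.258 = 3.10, on 22 df.
- Power from the noncentral t: 0.842, which matches. With m = 8 it would be 0.93, which does not.

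**Adding the first score to the primary model.** Let r be the correlation between the first simulated score and the oncologist's underlying (latent) level in clinic. The article gives no value, so r is an assumption.
- The variance of an oncologist mean becomes v = 0.20(1 − r²) + 0.20, with 21 df.
- The coefficient must be estimated, and the score will differ by chance between arms. On average this inflates the variance by 1 + 1/(24 − 4) = 1.05.

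Power at ICC 0.20, from v alone and then with the 1.05 factor (simulation of the covariate model agrees with the latter):
- r = 0: v = 0.400; 0.84, then 0.82
- r = 0.3: v = 0.382; 0.86, then 0.84
- r = 0.45: v = 0.3595; 0.88, then 0.86
- r = 0.5: v = 0.350; 0.88, then 0.87
- r = 0.7: v = 0.302; 0.925, then 0.91

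Break-even, setting aside the lost degree of freedom: 1.05(0.40 − 0.20r²) = 0.40 gives r² = 0.095, so r is about 0.31.

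How large might r be? If one simulated encounter had a reliability near the adopted ICC, r could not exceed sqrt(0.20) = 0.45, a gain of about 2 points. Standardization of the encounter could raise that ceiling. Note that r is not the correlation with the observed four-patient mean, which is smaller: r × sqrt(0.20/0.40) = 0.71r.

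At higher ICCs, same method with the 1.05 factor:
- ICC 0.40: 0.71 unadjusted; 0.72 at r = 0.3, 0.78 at 0.5, 0.87 at 0.7
- ICC 0.60: 0.61 unadjusted; 0.62, 0.69 and 0.82

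**Simulated encounters.** With two time points, time by condition is the two-sample test on change. For unit variance at both assessments and pre-post correlation rho (assumed):
- change score: 2(1 − rho), 22 df
- ANCOVA: 1 − rho², 21 df
- ratio: (1 − rho²)/[2(1 − rho)] = (1 + rho)/2

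Illustrative power, d = 0.8, 12 per arm, change score against ANCOVA:
- rho = 0.3: variance 1.40 against 0.91; 0.35 against 0.50
- rho = 0.5: 1.00 against 0.75; 0.47 against 0.58
- rho = 0.7: 0.60 against 0.51; 0.68 against 0.74

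With the 1.05 factor the ANCOVA figures become about 0.48, 0.56 and 0.72, still ahead of the change score. The ordering would reverse only where 1.05(1 + rho)/2 exceeds 1, at rho above about 0.90. Below rho = 0.5 the change score is weaker than ignoring the first score altogether (power 0.47).

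**The case against.** The strongest reply is that nothing here is wrong. The multilevel model is valid, 0.84 exceeds the 80% target, and an optional prognostic covariate can be left to a fuller document. The first two points stand. The third stands in part: the article does list the variables it adjusts for and does name the repeated-measures ANOVA, so these are stated choices that can be improved.

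The primary gain is uncertain, and that stands too. No correlation is given. The first encounter is a single scripted one with a deliberately passive actor-patient starting first-line treatment, whereas clinic consultations include evaluative ones and many tumour types. Training intervenes in one arm and may weaken the correlation there. Working status, already adjusted for, may absorb part of what the score would explain.

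The rule on adjusting for baseline differences might seem to admit the score. It would do so only if the arms happened to differ on it, and the variables named are patient-level. That is selection on observed imbalance, not prespecified adjustment.

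A reader might also infer three stronger things that the article does not support:
- That the trial is underpowered, or its power misstated. The figure reproduces.
- That leaving the score out biases the training effect. Oncologists are randomized, so chance imbalance in prior skill is random error, which the oncologist-level standard error already reflects.
- That between-oncologist variation is the main threat to power because ICCs reach 0.60. The article says most were 0.20 or lower, and reports 0.19 in a sample meeting the same eligibility criteria.

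**Conclusion.** The point holds as one of efficiency, not validity.

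For the simulated encounters, confidence is high. ANCOVA has the smaller variance at any plausible pre-post correlation, by the factor (1 + rho)/2 before a small estimation cost. The power figures are illustrative, because d = 0.8 was adopted for the clinic outcome and not for this one.

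For the primary training comparison, confidence is moderate. The change in power at ICC 0.20 runs from a loss of about 2 points at r = 0, through nil near r = 0.3, to a gain of about 3 points at r = 0.5 and 7 at r = 0.7. It is larger if the ICC is higher. These figures assume exactly four no-aid patients per oncologist and no overlap between the score and working status. A gain in the primary model should not be presented as assured.

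**What to change.** Before any comparison by arm:
- Prespecify the first-assessment OPTION12 score as an oncologist-level covariate in the OPTION12 model, and the first-assessment 4SDM score in the 4SDM model. Apply this to the training comparison and to combination versus usual care, whether or not the arms differ on the score.
- Replace the repeated-measures ANOVA by ANCOVA of the second simulated score on condition, first score and working experience. Treat the observed general communication skills in the simulated encounters, which share that analysis, in the same way.

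The cost is wording only, since the data are already collected. Statistically it takes one of 22 degrees of freedom in the primary comparison, and about 1 to 2 points of power there if the score turns out not to be predictive. The sample size and the stated 0.84 need no change.

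### Beyond two fixed stratification variables, covariates are chosen by testing for baseline imbalance, which costs precision and leaves part of the primary model open

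*Protocol article*

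**What the plan says.** Under Statistical methods, Primary outcome, the protocol article lists what is compared: "Baseline differences across arms on background characteristics (patient age, gender, educational level) as well as patients’ baseline measures". These "will be examined with the appropriate statistical tests (ANOVA, Chi-squared tests). All analyses of effectiveness will be controlled for differences between arms at baseline". In full, the second of these sentences begins "All analyses of effectiveness will be controlled for differences between arms at baseline as well as the two stratification variables (working status oncologist, type of" and ends with the word consultation. Two covariates are thus always in the model, and the others enter according to the observed differences. No threshold for a difference is given, and no other criterion for adding a covariate is stated.

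The same section opens by requiring clustering for the outcome: "To account for the hierarchical nature of the data, i.e. patients nested within oncologists, multilevel regression analysis will be used". Nothing comparable is said of the baseline tests.

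On timing, Recruitment (Patients) says that randomisation follows directly on oral consent, and that the package sent afterwards tells patients their condition and contains the aid where allocated. Procedure and time line says that the T0 questionnaire is posted at inclusion and brought completed to the consultation. Table 2 places QLQ-C30, STAI, the anxiety VAS, fighting spirit and helplessness/hopelessness at T0.

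**The concern.** A test for baseline imbalance asks whether a difference between arms is larger than chance would produce. It does not ask whether the variable is related to OPTION12. Used as a selector, it can add covariates that explain nothing and leave out prognostic ones that happen to balance, although adjusting for the latter is where the precision lies. It also leaves part of the primary model unknown until the arms have been compared.

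Two features add to this. Training is allocated by oncologist, so a test that treats patients as independent has the wrong error rate for any characteristic that clusters by oncologist. And T0 measures are collected after allocation, at a point when patients may already know their condition and hold the aid. A T0 difference in anxiety, fighting spirit or helplessness may then be an early effect of the aid, and controlling for it because it differs could take away part of the effect that the trial is meant to estimate.

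**Working it through.** **1. The plan's own power figure.** Inputs from Sample size: "we adopted an effect size of d = 0.8 in the sample size calculation"; ICC 0.20; 12 oncologists per arm; 8 patients each; "two-sided t-test taking into account clustered data"; "along with a power of >80% and α of 0.05". The training contrast uses patients without the aid, about 4 of the 8 per oncologist.
- Patients per arm: 12 × 4 = 48.
- Design effect: 1 + (4 − 1) × 0.20 = 1.6. Effective n: 48 / 1.6 = 30.
- Noncentrality: 0.8 / √(2/30) = 3.098, with 24 − 2 = 22 degrees of freedom.
- Power = 0.8415, which reproduces the stated 0.84. The sample size is not in question.

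**2. Chance flags with independent data.** Assume 5% per test.
- Three named characteristics: 1 − 0.95³ = 0.143.
- Eight candidates (the three plus the five T0 measures in Table 2, counting QLQ-C30 once): 1 − 0.95⁸ = 0.337.
- If the five T0 measures correlate at 0.3 to 0.5 (assumed), the eight-candidate figure falls to about 32% to 30%.

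**3. Effect of ignoring clustering.** Simulation of 24 oncologists × 8 patients, half with the aid, 20,000 runs, covariate ICC assumed:

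| Covariate ICC | Four-arm ANOVA, false-flag rate | At least one of 8 (independent) | Two-arm test, aid contrast |
|---|---|---|---|
| 0 | 5.0% | 34% | 4.7% |
| 0.05 | 6.6% | 42% | 4.8% |
| 0.10 | 8.6% | 51% | 4.1% |
| 0.20 | 13.0% | 67% | 3.0% |

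A two-arm test within the training contrast has size 2 × [1 − Φ(1.96 / √(1 + 3 × ICC))], which is 6.8%, 8.6% and 12.1% at ICC 0.05, 0.10 and 0.20, close to the ANOVA column.

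**4. Consequence for the training contrast.** Simulation of 12 against 12 oncologists with 4 patients each, 40,000 runs, one patient-level covariate with assumed ICC 0 or 0.10, residual outcome ICC 0.20, d = 0.8 for power and 0 for type I error. The test-selected analysis adjusts only when an unclustered two-arm test of the covariate gives p < 0.05. Ranges cover the two covariate ICCs.

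| Assumed correlation with outcome | Power, fixed | Power, test-selected | Type I, fixed | Type I, test-selected |
|---|---|---|---|---|
| 0.3 | 0.874 to 0.876 | 0.852 to 0.860 | 0.051 to 0.052 | 0.048 to 0.050 |
| 0.5 | 0.928 to 0.930 | 0.871 to 0.881 | 0.049 to 0.052 | 0.045 |
| 0.7 | 0.985 | 0.895 to 0.919 | 0.050 to 0.051 | 0.035 to 0.039 |

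The loss is about 2 points at 0.3, 5 to 6 at 0.5 and 7 to 9 at 0.7.

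**5. Timing of T0.** Set side by side, Recruitment and Procedure give this order: oral consent, randomisation, package disclosing the condition, with T0 sent at inclusion and returned at the consultation. Nothing requires T0 to be completed before the patient learns the condition.

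**The case against.** The strongest defence has four parts.

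- Selection by p-value is a reading of two adjoining sentences. No threshold is written, and a condensed article may leave it to a fuller plan. That is fair, and the 5% used here is an assumption. But the article does state a rule, and differences between arms are its only stated basis for adding covariates.
- Adjusting for an observed imbalance has some value. In the simulation at correlation 0.5, samples with a flagged covariate had a type I error of 12.5% to 13.8% unadjusted and 4.7% to 4.9% adjusted. This stands, but a fixed covariate gives the same protection in every sample.
- The wording about appropriate tests does not expressly exclude allowance for clustering. True, but the two methods named are the ordinary ones.
- Power with test-selected adjustment stayed at 0.85 or above, so the trial is not underpowered by this rule. That also stands: what is lost is available precision.

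A reader might infer more than the documents support. The whole primary model is not data-driven: outcome, contrasts, multilevel form and two covariates are fixed. The unclustered tests do not flag too often everywhere: for the aid, randomised within oncologist, they are mildly conservative. A two-group trained-versus-untrained test on all 8 patients per oncologist would flag 9% to 21% at the same ICCs, but the article states a comparison across arms, and its primary training contrast uses about 4 patients per oncologist.

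**Conclusion.** The point holds for every covariate other than oncologist working status and type of consultation. The rule selects on imbalance instead of prognosis, uses tests with no stated clustering term, and leaves part of the model undetermined until the arms are compared.

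The size depends on assumptions that the documents do not supply: the 5% threshold, the count of eight candidates, the covariate ICCs and the covariate-outcome correlation. If no available covariate correlates with OPTION12 at 0.3 or more, little power is at stake and the issue is mainly prespecification.

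It may be tempting to conclude that the primary test is anti-conservative because its p-value ignores the selection step. The calculations do not support that: type I error under selection was 0.035 to 0.050.

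The T0 point is separate and rests on the order of events in the article. It shows that bias in the aid contrast is possible, and its size cannot be computed from the documents. It should be corrected before the analysis, but it does not threaten the design.

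**What to change.** Replace the two sentences with a fixed rule:

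- Delete significance testing of baseline differences as the means of choosing covariates, and report baseline characteristics by arm descriptively.
- Whatever the observed balance, adjust the primary analyses for the two stratification variables plus patient age, gender and education. Age is asked by telephone and gender is known at referral. Education is recorded at T0 but is not plausibly altered by allocation.
- For the training contrast, add the oncologist's OPTION12 score from the first standardized patient assessment, which precedes training. Confirm that it also precedes disclosure of the oncologist's allocation, which the article does not say.
- Do not adjust the primary outcome for T0 anxiety, fighting spirit or helplessness.
- Label any further adjustment, including hospital, as a sensitivity analysis.

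The cost is one paragraph of wording, with no change to the 192 patients. There are two downsides. A chance imbalance in an unlisted variable is dealt with only in a sensitivity analysis. And each oncologist-level covariate uses one of about 22 degrees of freedom, which is why hospital is not made mandatory.
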